#### Quality Control Analysis

Data from group 1 will be used for quality control of the DFI measurement system. Specifically, using SCSA for DFI and HDS measurements, we will evaluate intraday, interday, and interfacility variability using quality control semen samples. Given that SCSA-derived DFI values can be influenced by the assay protocol, instrument settings, and gating strategy, this quality control step is required before the main association analyses [14,117,118]. After evaluating measurement validity, the flow cytometry gating settings will be fixed to ensure measurement reliability. Using data from group 1, we will confirm the distribution in young, healthy men; exclude outliers; and describe the reference value range.

#### Image Information Analysis

For the primary analysis, predefined microscopic sperm image-/video-derived summary variables will be assessed for association with the continuous DFI (primary outcome measure) as a preliminary proof-of-concept evaluation of whether image/video data contain information relevant to sperm DNA integrity. Associations with the continuous DFI will initially be assessed using correlation analyses and simple linear regression. When the DFI is categorized using prespecified literature-informed thresholds or a study-specific exploratory candidate threshold, simple logistic regression will be used as a secondary exploratory analysis. Any predictive modeling (including AI approaches) will be considered exploratory and will be specified in subsequent phases after database expansion. Exploratory image-DFI association analyses will be reported separately by group. If any additional pooled participant-level analysis across groups 1 and 2 is performed, the nonoverlapping dataset described earlier will be used.

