## Methods

### Study Design

The study has been registered in the University Hospital Medical Information Network Clinical Trials Registry (UMIN-CTR; #UMIN000060395; registration date: January 18, 2026; disclosure date: January 19, 2026).

This is a multi-institutional cross-sectional study with clinical data collection centralized at a single site to ensure high-quality standardization. One of the aims is to construct a foundational database capable of supporting future methodological development (including potential AI approaches), external validation, and generation of new hypotheses. To this end, we prospectively and systematically collected multimodal information (semen analysis, physical measurements, and questionnaires) centered on microscopic sperm image/video data obtained from apparently healthy community-based adult men, together with biological samples (semen, blood, and urine).

A characteristic of this study is the use of two participant groups with different inclusion criteria according to the analytic purpose. Participants in group 1 were recruited to ensure the reproducibility and stability of the DFI testing method. By minimizing confounding factors that may adversely affect sperm quality, such as aging, obesity, underweight, and smoking, and by limiting the group to men with a high ejaculation frequency, we aimed to identify a population expected to maintain high spermatogenic function. In this group, only semen was collected as a biological sample. In contrast, participants in group 2 were included to ensure broader representation of potential risk factors associated with a worsening DFI in otherwise apparently healthy community-based volunteers. In this group, in addition to semen, blood and urine samples were collected to examine the effects of nutritional and endocrine profiles and environmental exposure.

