### Statistical Analysis

#### Descriptive Statistics and Data Preprocessing

Continuous variables will be summarized as means (SDs) and/or medians (IQRs), depending on the distribution characteristics, and categorical variables will be summarized as frequencies (percentages) [106]. The DFI will be treated as a continuous variable. Categorization using literature-informed thresholds (eg, 15% and 27%) [107-110] will also be used in secondary exploratory analyses. In addition, if data characteristics permit, a study-specific candidate threshold will be explored using receiver operating characteristic (ROC) analysis against a prespecified binary semen quality classification based on the lower fifth percentile values for basic semen parameters described in the 6th Edition of the *WHO Manual for Human Semen Analysis* [94,111,112]. Any such data-driven threshold will be considered hypothesis generating only [113].

No formal between-group inferential comparison between groups 1 and 2 is a primary objective of this study. Any comparison of baseline characteristics between the two groups will therefore be descriptive/exploratory only. If participant overlap between groups is present, co-enrolled individuals will be counted only once in such cross-group summaries or in any pooled participant-level analysis requiring independence. Under the primary handling rule, the group 1 record will be retained and the corresponding group 2 record excluded, because group 1 had stricter eligibility criteria and a quality control purpose. Alternative handling rules, such as retaining the group 2 record or excluding co-enrolled participants entirely, may be examined as sensitivity analyses. This issue does not affect the main group-specific analyses, in which group 1 is used for DFI quality control and group 2 for exploratory association analyses.

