All statistical tests will be two-sided and interpreted using a nominal significance level of *P*<.05. However, the secondary analyses are exploratory and involve multiple related comparisons and sensitivity analyses. Thus, emphasis will be placed on effect sizes, 95% CIs, and consistency of direction rather than on statistical significance alone, and no formal multiplicity adjustment is planned. As exposure indices (eg, environmental chemicals) may generally exhibit skewness, transformations (eg, logarithmic transformations) will be considered according to the distribution [114]. For urinary indices, a correction using urinary creatinine or specific gravity will be applied [115,116].

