## Results

Participant recruitment began on January 18, 2026, and recruitment and sample/data collection were completed on February 21, 2026. Final enrollment yielded 25 group 1 records and 103 group 2 records. In addition, 4 individuals contributed records to both groups; thus, the study comprises 124 unique participants overall. For any cross-group descriptive comparison or pooled participant-level analysis requiring independence, these co-enrolled cases will be handled using the prespecified de-duplication rule described in the *Statistical Analysis* section. The last participant visit occurred on February 21, 2026. Biological samples will be sequentially analyzed after collection, and exploratory assays are planned to continue throughout the study period until March 2028. The findings of this study will be disseminated through domestic and international academic conferences and journal publications. After completion of biospecimen assays, the primary association analysis (between sperm image/video data and the DFI) and exploratory analyses of secondary outcome measures will be conducted, with primary analyses planned to be completed by March 2028.

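### Simple logistic regression on DFI cut at thresholds such as 15% and 27% has no sparse-event safeguard; in group 1 (25 low-risk men) the fits may often fail or be inflated, mainly at the higher cut.

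*Protocol article*

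**What the plan says.** All references are to the protocol article.

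- **Image Information Analysis.** The primary analysis relates image and video summary variables to continuous DFI by correlation and simple linear regression. For DFI cut at literature-informed or study-specific thresholds, "simple logistic regression will be used as a secondary exploratory analysis". The same section adds: "Exploratory image-DFI association analyses will be reported separately by group".
- **Descriptive Statistics and Data Preprocessing.** "Categorization using literature-informed thresholds (eg, 15% and 27%) [107-110] will also be used in secondary exploratory analyses". The section also describes group 1 as serving DFI quality control and group 2 as serving exploratory association analyses. It asks that effect sizes, 95% confidence intervals and consistency of direction carry more weight than significance alone.
- **Abstract (Methods) and Study Objectives.** Image-DFI association analyses are placed in both groups.
- **Study Design.** Of group 1: "we aimed to identify a population expected to maintain high spermatogenic function".
- **Results.** "Final enrollment yielded 25 group 1 records and 103 group 2 records". Four men are in both groups; "thus, the study comprises 124 unique participants overall".
- **Exploratory Analysis.** Adequate data completeness and enough informative observations are required for multivariable models. No such condition is set for the simple models.

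**The concern.** A logistic model needs men on both sides of the cut. With none above it, no odds ratio exists. With one or two, the predictor may separate the classes completely and the maximum-likelihood estimate is infinite. With a handful, the estimate exists but is biased away from 1.

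Group 1 was chosen by age, BMI, smoking status and ejaculation frequency so that poor sperm quality would be uncommon, and it has only 25 men. It is therefore the group in which a model of high DFI is hardest to fit. Under Sample Size, the article says the findings will guide variable prioritisation and sample-size planning for later phases. An overstated odds ratio used for planning would make a later study too small.

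**Working it through.** **Figures to reproduce.** The article gives no event count, prevalence or power for categorical DFI. The one checkable count agrees: 25 + 103 − 4 = 124.

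**Inputs.**
- From the article: n = 25 and n = 103, taken as upper limits because a record without DFI or images cannot contribute; one predictor per model.
- Assumed: the share p above the cut, 2% to 30%; a standard normal predictor; a true odds ratio of 2 per SD (log OR = ln 2 = 0.693); ordinary maximum likelihood, which is the usual meaning of logistic regression without qualification.

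**Step 1: number of men above the cut (exact binomial).** Expected number = n·p. P(none) = (1 − p)^n. P(at most one) = (1 − p)^n + n·p·(1 − p)^(n−1). P(fewer than 5) = sum over k = 0 to 4 of C(n,k)·p^k·(1 − p)^(n−k).

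| n | p | Expected | P(none) | P(at most one) | P(fewer than 5) |
|---|---|---|---|---|---|
| 25 | 3% | 0.75 | 0.97^25 = 47% | 83% | 99.9% |
| 25 | 5% | 1.25 | 0.95^25 = 28% | 64% | 99% |
| 25 | 10% | 2.5 | 0.90^25 = 7% | 27% | 90% |
| 25 | 20% | 5.0 | 0.80^25 = 0.4% | 3% | 42% |
| 103 | 3% | 3.1 | 0.97^103 = 4% | 18% | 80% |
| 103 | 5% | 5.2 | 0.95^103 = 0.5% | 3% | 41% |
| 103 | 10% | 10.3 | <0.1% | <0.1% | 2% |

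**Step 2: fits that do not exist (simulation, 1,500 to 3,000 data sets per setting in most runs).** A fit was counted as inestimable if no man was above the cut or the predictor separated the classes completely.
- Group 1: about 54%, 34% and 10% at p = 3%, 5% and 10%. Separate runs gave 53%, 32–34% and 11%. At 20% the figure is 1–2%, and at 30% it is 0.2%.
- Group 2: 13.5% at p = 2%, about 2% at 4%, 1% at 5%, and about 0% from 8% upward.

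**Step 3: size of the estimates when they exist.**
- Group 1, p = 3% to 30%: mean log OR 0.86 to 1.01 against 0.693. The ratios are 0.86/0.693 = 1.24 and 1.01/0.693 = 1.46, so the excess is about 25% to 45%. Medians (p = 4% to 30%) are 0.65 to 0.79, so the excess lies mainly in the upper tail. The median ratio of upper to lower 95% limit for the odds ratio is about 65 at p = 4%, 26 at 10% and 12 at 20%.
- Group 2: mean log OR 0.836 at p = 2% (21% too large), 0.775 at 4% (12%), 0.770 at 5% (11%) and 0.735 at 10% (6%). The interval ratio falls from 19 at 2% to 4.3 at 10%.

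**Step 4: Firth penalised regression on the same question.** In group 1 the mean slope is 0.61 to 0.73 across the simulations. In group 2 it is 0.67 to 0.71, against 0.73 to 0.76 for maximum likelihood over p = 4% to 30%. Firth removes separation and most of the bias. It cannot rescue a data set with no man above the cut, so a minimum count is still needed.

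**The case against.** Several points on the other side have force.

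- **The prevalence is unknown.** The documents give no share above 15% or 27%, so the failure rates are conditional. This stands.
- **A reader might infer that the categorical models will often fail or be badly inflated in both groups and at both cuts.** The calculations do not support that. Group 2 fits almost always exist from 5% upward, with small bias, and group 1 fits usually exist at 20–30%, which the 15% cut might give.
- **Much of the inflation is imprecision.** Group 1 medians are close to the truth, and the article gives weight to 95% confidence intervals, which would expose unstable estimates. This limits the harm. It does not justify an estimator with a known upward bias when a better one is to hand.
- **Group 1 has little route into decisions.** Candidate predictors are sought in group 2, mainly with continuous DFI, and the Strengths and Limitations section asks for caution with unstable findings. This also stands.
- **Logistic models in group 1 are inferred.** The abstract ties both groups to the continuous analysis, and its categorical sentence names no group. Yet the logistic sentence and the by-group reporting sentence stand in the same section, with no exception for group 1.
- **The estimator could be left to an analysis plan.** The article names none. But it does fix the model type and by-group reporting, and limits its adequacy condition to multivariable models. A specific, better method is available for what it fixes.

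**Conclusion.** The point holds in a limited form. As written, the article leads to simple logistic fits in 25 low-risk men with no rule for sparse events. If about 3% to 10% of them exceed the cut, roughly 54% down to 10% of maximum-likelihood fits would not exist. Over 3% to 30%, those that do exist are too large on the log scale by about 25% to 45% on average. These figures rest on the assumed prevalence, a true odds ratio of 2 per SD, a normally distributed predictor and ordinary maximum likelihood. The concern is greatest for the 27% cut in group 1, modest in group 2 when fewer than about 5% exceed the cut, and slight otherwise. The analysis is secondary and exploratory, so this is a cheap improvement and no threat to the study's main result.

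**What to change.** **Group 1.** Report only the number and proportion of men above each cut, with an exact confidence interval, and fit no logistic model. This matches the quality control role that the article gives the group. It remains informative: 0 of 25, for instance, has an exact two-sided 95% upper limit of 1 − 0.025^(1/25) = 13.7%.

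**Group 2.** Use Firth penalised logistic regression with profile-likelihood confidence intervals at every cut. Give counts only when very few men, for example fewer than 5, fall in the smaller class. The value 5 is a working choice; what matters is to set it before the DFI results are seen. Continuous DFI remains the basis for prioritising variables, as the article already intends.

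**Cost.** Two or three sentences of plan wording and standard software. Group 1 would have no categorical odds ratios, which it could seldom support. In group 2 the minimum count would also withhold a model in about 41% of cases if 5% of men exceed the cut, and in about 2% if 10% do.

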#### Exploratory Analysis

For group 2 data, associations among the DFI, microscopic sperm image/video data, and clinical variables will be analyzed to identify candidate predictors and confounding factors for image-based analyses. Core analyses will prioritize standard semen parameters, questionnaire data, and physical measurements. The DFI will be analyzed primarily as a continuous outcome, with secondary analyses using thresholds [107-110]. Building on the reference values established in the quality control analysis, we may explore a study-specific DFI threshold against the WHO criteria [93] using ROC analysis. The area under the ROC curve and Youden index–derived cut points will be reported as hypothesis-generating results.

Candidate variables will first be examined using correlation analyses, group comparisons, or simple linear/logistic regression, as appropriate to variable type. Age and recruitment-related participant characteristics (eg, employment status, shift work, education, and income) will also be examined as candidate covariates or stratification factors to evaluate potential selection-related bias. The data of participants selecting “prefer not to answer” for education or income will be retained in descriptive analyses, and sensitivity analyses will compare alternative handling of these responses (eg, separate-category vs exclusion approaches). Given that a population-based sampling frame is not available, these analyses are intended to assess robustness rather than fully remove selection bias. Multivariable linear or logistic regression models will be considered only when data completeness and the number of informative observations is adequate. To reduce overfitting, the number of predictors simultaneously included will be restricted, with priority given to variables selected based on prior knowledge and univariable results. Multicollinearity will be assessed using the variance inflation factor, with values >3 considered to indicate potential concern. In such cases, we will preferentially retain representative variables or use dimension reduction, clustering, or mixed-exposure approaches as exploratory analyses.

#### Missing Data and Sensitivity Analysis

Participants with missing data for primary outcome measure analysis (DFI or images) will be excluded from the primary analysis, and the reasons for missingness will be described. Considering that the status of questionnaires or samples, such as self-reports of spilling all or part of the sample during collection [119] or recent infectious diseases (eg, a cold, influenza, or COVID-19) with or without a high fever (≥38°C) within the past 3 months [120,121], may affect the results, sensitivity analyses excluding such participants will be conducted, as necessary. If azoospermic samples are observed, sensitivity analyses will be performed both including and excluding them because their underlying etiologies cannot be fully characterized in this non-clinic-based setting [122].

### Ethical Considerations

The study protocol underwent central ethical review and was approved by the Institutional Review Board (IRB) of the Osaka Pharmacology Clinical Research Hospital (IRB approval #R01114a; committee review date: December 18, 2025; notification date: December 19, 2025) in accordance with the Ethical Guidelines for Medical and Biological Research Involving Human Subjects in Japan. AIST, which leads protocol development and overall study governance, does not accept reliance on another institution’s review. Hence, independent approval was additionally obtained from the IRB of AIST (IRB approval #Life 2025-0618; review completion date: January 6, 2026; notification date: January 7, 2026). Based on the central review, study implementation or institutional approval was also obtained from the University of Tsukuba Hospital (approval #R07-275), the Tsukuba Gakuen Hospital (approval #25-23), the International University of Health and Welfare (approval #25-MB-18), the Nagoya University Graduate School of Medicine (approval #2025-0536; commission #2025-184), and the National Institute for Environmental Studies (approval #2025-024).

The study will be conducted in accordance with the Declaration of Helsinki and Ethical Guidelines for Medical and Biological Research Involving Human Subjects in Japan. Written informed consent was obtained from all participants after a full explanation of the study objectives, procedures, potential benefits, and risks. Questionnaire data and biospecimens were deidentified using a study identification code. The linkage key is retained only at the Osaka Pharmacology Clinical Research Hospital, and collaborating institutions and external laboratories receive coded data/samples only. Sensitive sexual and reproductive information was collected primarily through self-administered questionnaires, where participants were allowed to select a “prefer not to answer” option to ensure their autonomy and minimize psychological distress, consistent with a recent study [123]. The participants received reimbursement for study-related expenses to reduce the burden of transportation and time commitment rather than as an incentive for participation: JPY 10,000 (~US $63) for group 1 and JPY 15,000 (~US $94) for group 2 (JPY 5000, ~US $31, on the explanation day and JPY 10,000, ~US $63, on the study day). Individual research results, including incidental findings, are not routinely returned because the assays were conducted for research purposes and may not be clinically interpretable at the individual level. This policy was explained during the informed consent process.

## Results

Participant recruitment began on January 18, 2026, and recruitment and sample/data collection were completed on February 21, 2026. Final enrollment yielded 25 group 1 records and 103 group 2 records. In addition, 4 individuals contributed records to both groups; thus, the study comprises 124 unique participants overall. For any cross-group descriptive comparison or pooled participant-level analysis requiring independence, these co-enrolled cases will be handled using the prespecified de-duplication rule described in the *Statistical Analysis* section. The last participant visit occurred on February 21, 2026. Biological samples will be sequentially analyzed after collection, and exploratory assays are planned to continue throughout the study period until March 2028. The findings of this study will be disseminated through domestic and international academic conferences and journal publications. After completion of biospecimen assays, the primary association analysis (between sperm image/video data and the DFI) and exploratory analyses of secondary outcome measures will be conducted, with primary analyses planned to be completed by March 2028.

## Discussion

### Summary

The principal contribution of this initial phase of N-SEED is the establishment of a standardized methodology for constructing a prospective multimodal database that links sperm microscopy image/video data with the DFI and a wide range of environmental, physiological, and lifestyle covariates. Compared to much of the existing image analysis literature on male infertility, this protocol incorporates environmental chemicals, endocrine profiles, and lifestyle-related measures, alongside semen microscopy [18-20]. In this initial phase, the resulting resource is intended to support feasibility-oriented association analyses, confounder assessment, and hypothesis generation. It is not intended to provide a clinically deployable AI tool or definitive evidence regarding predictive performance.

### Comparison With Prior Work

Most current AI applications in male infertility have focused on relatively narrow tasks, such as sperm morphology, motility, sperm retrieval, or in vitro fertilization-related prediction. Recent reviews consistently note methodological heterogeneity, limited multimodal integration, and insufficient multicenter external validation as major barriers to clinical implementation [18-20]. More broadly, the literature on semen quality has also been affected by heterogeneous source populations, retrospective designs, and differences in laboratory methods, which complicate interpretation across studies [2,4].

Overall, these prior studies indicate two relevant gaps. First, datasets directly linking standardized sperm microscopy image/video data with a functional marker of sperm DNA integrity, such as the DFI, are limited [18-20]. Second, environmental, endocrine, physical, and lifestyle variables that may confound or contextualize image-based associations are often incompletely represented in existing datasets [18-20].

The protocol is specifically designed to address these methodological gaps by prospectively collecting standardized sperm microscopy image/video data, together with the SCSA-based DFI and broader covariates in apparently healthy community volunteers. By recruiting outside infertility clinics, the study attempts to reduce, although not eliminate, the disease-related selection structure that characterizes many retrospective clinic-based datasets. Accordingly, the immediate contribution of this initial phase is methodological: to establish standardized acquisition procedures, characterize data completeness and measurement variability, and support feasibility-oriented analyses of associations between image-/video-derived variables and the DFI. Questions of model development, threshold validation, and external generalizability remain for later expanded phases.

